### Procedures, recruitment, randomisation and collection of baseline data

All women with a singleton pregnancy who present at one of the participating clinics will be referred to an obstetrician or a specifically appointed research nurse/midwife for counselling. Eligible women receive participant information. After written consent, they are randomised by means of a web-based application. Stratification will be applied for previous vaginal birth (nullipara versus multipara) and for centre. Randomisation will be in a 1:1 ratio for induction of labour or expectant management.

Patients that withhold consent for randomisation are asked permission for data collection on pregnancy outcome. Participation to the quality of life study and long-term follow up (Child Behavioural Check Lists-CBCL and Ages and Stages Questionnaire-ASQ) is asked separately.

Baseline demographic, past obstetric and medical histories will be recorded for all women. Cervical length will be measured at the time of randomisation. The quality of life questionnaires are filled out before randomization, after randomization, 6 weeks postpartum and 6 months postpartum. The questionnaires contain the Hospital Anxiety and Depression Scale (HADS), EuroQoL 5D3L, Short Form (SF-36), Symptom Check List (SCL-90), and questions on background characteristics, intervention preparedness, risk perception and experience with the current pregnancy.

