### Outcome measures

The primary outcome measure will be a bad composite neonatal outcome. Adverse neonatal outcome will be defined as death before hospital discharge, a 5-minute Apgar score < 7, an umbilical artery pH < 7.05 or admission to the neonatal intensive care. Secondary outcome measures are mode of delivery and time until delivery, length of admittance at the neonatal intensive care, maternal morbidity, hospitalisation of the mother for fetal and maternal surveillance, quality of life, and costs. In the present proposal, no funding is asked for long term follow-up of the child, yet. However, if additional funding can be obtained children's behavioural-, and neuro development will assessed by administering with a postal enquiry the Child Behaviour Checklist-CBCL and Ages and Stages Questionnaire- ASQ by their parents after 2 years.

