#### Data analysis

Data will initially be analysed according to the intention to treat method. The main outcome variable, 'bad neonatal outcome', will be assessed by calculating rates in the two groups, relative risks and 95% confidence intervals as well as numbers needed to treat.

Time to delivery will be evaluated by Kaplan-Meier estimates, with account for differing durations of gestation at entry, and will be tested with the log rank test. The other secondary outcome measures will be approached similarly to the primary outcome measure. The analysis will be stratified for parity and centre.

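### Quality-of-life scores and hospital days are sent to the binary primary analysis, which needs cut-points the protocol does not give and makes no use of the pre-randomisation score

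*Protocol article*

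**What the plan says.** The Data analysis section says that the primary outcome, a yes/no composite, "will be assessed by calculating rates in the two groups, relative risks and 95% confidence intervals as well as numbers needed to treat". One secondary outcome then receives a method of its own: "Time to delivery will be evaluated by Kaplan-Meier estimates", with a log rank test. For the remainder there is a single rule: "The other secondary outcome measures will be approached similarly to the primary outcome measure". The only adjustment named is stratification: "The analysis will be stratified for parity and centre".

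The Outcome measures section shows what this rule covers: "Secondary outcome measures are mode of delivery and time until delivery, length of admittance at the neonatal intensive care, maternal morbidity", followed by "hospitalisation of the mother for fetal and maternal surveillance, quality of life, and costs".

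The section on procedures, recruitment and baseline data names four scored instruments for quality of life (HADS, EuroQoL, SF-36 and SCL-90) and their timing: "The quality of life questionnaires are filled out before randomization, after randomization, 6 weeks postpartum and 6 months postpartum". That is one measurement before randomisation and three after it.

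Two other sections bear on the point. Economic evaluation assigns costs a cost-effectiveness analysis. Non response and inclusion bias calls for imputation where follow-up data are missing.

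**The concern.** A rate, a relative risk and a number needed to treat are defined for an event. A scale score or a number of days is not an event until someone chooses a threshold, and the protocol gives none. An analyst who follows the sentence must invent cut-points, possibly after seeing data. An analyst who keeps the scores continuous departs from the published rule. Either way the choice is left open on outcomes that matter: maternal quality of life is a stated aim of the trial. If the neonatal outcome proves equivalent, as the design supposes, the secondary outcomes will carry much of the choice between induction and expectant management.

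The stated approach is also less precise than one the trial can already afford. It turns graded scores into two classes, and it makes no use of the score taken before randomisation.

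**Working it through.** **1. The plan's own figure.** The only sample size stated is 325 per arm, for the primary outcome. Inputs from Sample size calculations: rate p = 0.06 in both arms, margin 0.055, true difference 0, two one-sided Z tests at 0.05, power 80%.

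n = 2p(1−p)(z₀.₉₅ + z₀.₉₀)² / margin² = 2 × 0.06 × 0.94 × (1.645 + 1.282)² / 0.055² ≈ 319.3, so 320 per arm. At 325 per arm the power is 80.9%. The stated figure is reproduced closely, and nothing below changes it.

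**2. Which outcomes fit the rule.**

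| Secondary outcome | Type | Rates, relative risk, NNT? |
|---|---|---|
| Mode of delivery | categorical | yes, per category |
| Maternal morbidity | event | yes |
| Time until delivery | time to event | exempted; own method |
| Length of neonatal intensive care stay | days, skewed | only after a cut |
| Maternal hospitalisation | yes/no, or days | yes as yes/no; days only after a cut |
| Quality of life | scores, four occasions | only after a cut |
| Costs | skewed amount | only after a cut, but see Economic evaluation |

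**3. What a cut costs (assumed: normal score, split at the median).** The relative efficiency is 2/π = 0.637, so about 64% of the information is kept.

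**4. What baseline adjustment gains (assumed correlation r between pre-randomisation and follow-up score).** Residual variance is multiplied by 1 − r²:
- r = 0.5: 0.75, a cut of 25%
- r = 0.6: 0.64, a cut of 36%
- r = 0.7: 0.51, a cut of 49%

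**5. The two effects on one scale (assumed: standardised difference d = 0.25, two-sided 5%, 80% power).** For a continuous score, n = 2(1.960 + 0.842)²(1 − r²)/d² per arm, with r = 0 when baseline is not used. For a median split, the two proportions are Φ(0.125) ≈ 0.550 and Φ(−0.125) ≈ 0.450, entered in the usual two-proportion formula.

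| Analysis | n per arm for 80% power | Power at 325 per arm |
|---|---|---|
| Median split, rates | 396 | 72% |
| Continuous, no baseline | 252 | 89% |
| Continuous, baseline, r = 0.3 | 229 | 92% |
| Continuous, baseline, r = 0.5 | 189 | 96% |
| Continuous, baseline, r = 0.7 | 129 | 99% |

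The ratio 252/396 = 0.64 agrees with step 3. These rows take all 325 women per arm as contributing. Consent to the quality-of-life study is asked separately, so the actual number may be smaller.

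**The case against.** The strongest reply is that the wording is loose. Being approached similarly could mean only the same framework: intention to treat, a between-group estimate with a confidence interval, stratified analysis. The protocol orders no dichotomisation, and an article normally leaves covariates and repeated-measures models to a fuller plan. Mere silence would indeed be no finding. But this is not silence. The text makes a positive rule covering all remaining secondary outcomes, directly after exempting the one outcome whose authors saw that it needed something else. The primary approach to which it refers consists entirely of binary summaries.

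Several stronger readings are tempting, and the document does not support them:

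- **That the baseline quality-of-life score is discarded.** Nothing says so. The stated rule simply makes no use of it, and a fuller plan may.
- **That the analysis is impossible.** It is possible after dichotomising. The rule also fits mode of delivery, maternal morbidity and maternal hospitalisation taken as yes/no.
- **That costs will be reduced to a relative risk.** Economic evaluation gives them a cost-effectiveness analysis. The fault is only that the general sentence does not exempt them.
- **That neonatal stay will be compared among admitted infants only.** No such restriction is stated. It would rest on a small group chosen after randomisation (at most 0.06 × 325 = 19.5 per arm if every composite event were an admission), but the protocol does not propose it. The point is only that the population should be named.

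It is also fair to say that the efficiency figures are generic. No loss specific to this trial can be computed.

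**Conclusion.** The concern holds for the quality-of-life scores and for hospital days, neonatal and maternal. For these the stated method works only with cut-points the protocol does not supply, and for quality of life it leaves unused a baseline measurement that is already collected. It does not hold for the event-type secondary outcomes, and for costs it amounts to a missing cross-reference.

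On assumed values the size is material: about 64% of the information kept under a median split, and a further 25% to 49% of residual variance removable at correlations of 0.5 to 0.7. This rests on normality, a cut at the median and those correlations. Cuts elsewhere, skewed scores or weaker correlations would give other figures. The direction does not depend on the exact correlation: adjusting for a prognostic baseline score improves precision.

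The fault affects secondary outcomes only. The primary analysis and the sample size stand. It should be corrected, because doing so is nearly free and removes an open choice of thresholds.

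**What to change.** Replace the general sentence in Data analysis with four statements:

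1. Binary secondary outcomes (categories of mode of delivery, maternal morbidity, any maternal hospitalisation) are analysed like the primary outcome.
2. Quality-of-life scores are analysed as continuous, by ANCOVA at each time point or by a mixed model for repeated measures, adjusted for the pre-randomisation score and for both stratification factors, parity and centre. Missing questionnaires are handled consistently with the Non response and inclusion bias section.
3. Neonatal intensive care days and maternal hospital days are compared over all randomised, counting zero where there was no admission, by a mean difference with a confidence interval suited to skewed data, such as a bootstrap interval.
4. Costs are analysed as set out under Economic evaluation.

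ANCOVA and the mixed model are both acceptable; what matters is to name one in advance. The change is to wording, with slightly more analysis work. It needs no new data, no further participants and no change to the primary analysis, since the pre-randomisation questionnaires are already part of the schedule.

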#### Non response and inclusion bias

As non-response for follow up is overrepresented in certain outcome-related risk categories such as in non-native mothers, mothers with lower educational level and in mothers with boys, statistical methods that use imputation of missing data have to be applied [48]. To prevent inclusion bias all patients who were asked but decline randomisation, will be asked for permission to collect data on pregnancy outcome and further follow up according to the same schedule as the randomised patients.

### Economic evaluation

The aim of the economic evaluation is to compare optimality, in terms of costs and health effects, of both strategies. As the clinical study is based on equivalence design we hypothesize that there will be no relevant difference between maternal and neonatal outcome in the two strategies. The economic evaluation will be in the form of a cost-effectiveness analysis (CEA), in which the optimal strategy is defined as the strategy with the largest health gain at the smallest costs.

### Ethical considerations

This study has been approved by the ethics committee of the Leiden University Medical Centre (Ref. No. P04.210).

## Discussion

There is uncertainty about the management of IUGR at term, whether to leave the child in utero until spontaneous labour starts, or to prevent undernutrition by prolonged pregnancy in a poor intra-uterine environment by inducing labour. This latter treatment modality will most probably be at the cost of an increase in instrumental deliveries [46]. As optimal management of a pregnancy at term suspected to be complicated by IUGR remains unclear, it is a challenge to develop criteria for inducing delivery. An increase in fetal surveillance in these pregnancies (with normal umbilical artery studies) is thought to be associated with more inductions of labour and a shortening of gestational age [49]. Neonatal morbidity (and mortality) is low in term SGA neonates [3], nevertheless these neonates cannot be considered just "healthy small babies".

Although our primary aim is to study pregnancies complicated by IUGR, the inclusion criteria are obviously based on a suspicion of a SGA child, as we include women with a fetus with a Fetal Abdominal Circumference < 10^th ^centile or an Estimated Fetal Weight < 10^th ^centile. By patient's characteristics, such as ethnicity, maternal and paternal length as well as tests results as the amount of amniotic fluid or the Doppler of the arteria umblicalis, we will be able to evaluate which pregnancies are at risk for a poor neonatal outcome.

In summary, at the present, there is controversy as to which strategy is the best when IUGR at term is suspected. Whether to induce labour or to await spontaneous labour under strict fetal and maternal monitoring remains debatable because of a lack of evidence. Patients' management partly depends on the attending doctor and on local protocols. To resolve these issues, we will compare both strategies in the multi centre randomised trial – DIGITAT. In a pilot study carried out in one of the participating hospitals, we examined the feasibility of the DIGITAT-trial. Preliminary data from this small pilot show that the interval between randomisation and labour was 2 weeks shorter and birth-weight was 100 grams less in the pregnancies that were directly terminated by induction [50]. The results of the present DIGITAT-trial are expected in 2009.

## Abbreviations

IUGR – Intrauterine growth retardation

SGA – Small for gestational age

CBCL – Child Behavioural Check List

ASQ – Ages and Stages Questionnaire

NICU – Neonatal Intensive Care Unit
